**PROTOCOL SUMMARY**

**Protocol 003:** Randomized Double Blind Placebo Controlled Trial to Evaluate the Safety and lmmunogenicity of the Aventis Pasteur ALVAC-HIV (vCP205) Administered to the Groin Area versus the Deltoid Area

**Subjects:** Healthy adult subjects who have no identifiable higher risk behavior for HIV-1 infection.

**Number of Subjects:** 18 completing all visits to day 24 (completion of all baseline, vaccination, safety and immediate immune response visits) - based in past experience we will “over-enroll” (signing consent) up to a total of 24 to allow for subject or investigator initiated withdrawal.

Schema:

| Route/Volume of ALVAC-HIV (vCP205) or placebo | IMMUNIZATIONS | | | |
| --- | --- | --- | --- | --- |
|  | 1 (day 0) | 2 (day 7) | 3 (day 14) | 4(day 21) |
| Subcutaneous (groin)  or  Intramuscular (deltoid)  1 ml | ALVAC-HIV (vCP205) | ALVAC-HIV (vCP205) | ALVAC-HIV (vCP205) | ALVAC-HIV (vCP205) |
| placebo | placebo | placebo | placebo |

**Study period for each subject:** 14 months (starting at day –42 through week 52)

**Follow up period for each subject:** 26 months (includes 1 year of as needed subject-initiated visits and PCR testing)

Time period for trial: 2 years

**Safety Monitor:** [name]

Director, Center for Clinical AIDS Research and Education (CARE)

UCLA, School of Medicine

**Funding Agency:** National Institute of Allergy and Infectious Diseases

**Clinical Site:** University of California, Los Angeles

**Data Coordination:** University of California, Los Angeles

CONTACT LIST FOR INVESTIGATORS

UCLA School of Medicine

Center for HIV and Digestive Diseases

[name]

[name]

[name]

[name]. [contact]

Cellular Immunology and Cytometry Laboratory

[name]

[name]

[name]

[name]. [contact]

UCLA Center for Clinical AIDS Research and Education (CARE)

[name]

[name]

[name]

[name]. [contact]

Aventis Pasteur S.A.

[name]

[name]

[name]. [contact]

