### Twelve subjects will receive the vaccine, 6 in the groin area, subcutaneously (SQ) and 6 in the deltoid region intramuscularly (IM). Six subjects will receive placebo, 3 in the groin SQ and 3 in the deltoid region IM. The table shows two sets of probabilities for observing adverse events. *Visit-specific* probabilities refer to adverse events that have a common, independent rate of occurrence for each of the four vaccination visits, i.e. the relevant n is the total number of injections. *Patient-specific* probabilities refer to adverse events that affect a given proportion of subjects, i.e. the relevant n is the number of patients. The first pair of columns give probabilities of observing one or more and two or more adverse events in a particular 6 patient arm. The next pair of columns gives probabilities for observing events in the 12 patient treatment group as a whole. The final pair of columns gives these probabilities for all 18 patients in the trial.

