**7.0 RANDOMIZATION AND BLINDING**

This is a randomized, modified double-blind placebo-controlled study. The 18 subjects in the study will be randomized first into either the deltoid or groin group, then to the treatment or placebo arm. The randomization plan is based on three groups of six patients each so that within each sequential cohort of 6 recruited subjects, three will randomly be assigned to groin and the other three will receive deltoid immunization. Each of these subgroups will also be randomized so that two subjects will receive active treatment whereas the other will receive placebo. This approach was felt necessary to achieve a balanced design, even if the study does not recruit all planned subjects.

The vaccine and placebo have a slightly different appearance. In order to maintain the modified blind a trained RN or Nurse Practitioner will deliver the vaccine or placebo not otherwise associated with the study. The study staff will handle all processes relating to subject study participation, care and monitoring except for actual vaccination. Staff will remain in the immediate vicinity of the subject during vaccination.

- 1. **HUMAN SUBJECTS**

Each subject must be a human immunodeficiency virus type 1 (HIV-1) seronegative man or non-pregnant woman with a low risk profile for HIV-1, and at least 18 years old.

- 1. **Inclusion Criteria**

1. Age: 18 – 60 years of age.
2. Female or male (for females, negative serum pregnancy test at time of entry into the study and assurance of adequate, reliable birth control measures until at least 60 days after the final immunization or documentation of non-reproductive status e.g. record of tubal ligation).
3. At low risk for acquiring HIV-1 (no STD within one year of beginning trial, no history of injection drug use, no sex with an HIV infected individual or active injection drug user within six months of beginning trial, no unsafe sexual activity with unknown partners or mutually monogamous relationship with a known HIV seronegative partner (per subject report) for the last six months.
4. Normal history and physical examination.
5. Normal complete blood count, differential, ALT and creatnine.
6. Negative for HIV by an FDA approved blood test, negative hepatitis B surface antigen and anti-HCV or negative HCV PCR if anti-HCV positive.
7. Capable of giving informed consent.
8. Willing to abstain from receptive anal intercourse during the 14 months of the study

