**8.4.2 Investigator-initiated withdrawal**

The investigator may withdraw a subject from participating in this research if circumstances arise which warrant doing so. The investigator, [name], will make the decision and inform participants of these circumstances. This decision may be made either to protect participants’ health and safety, because a condition develops that places the participant in an exclusion category or because baseline responses will not permit an effective comparison with post-immunization results.

Experiences of grade 4 (potentially life threatening) will automatically exclude subjects from further participation in the trial. [name] and [name] will evaluate all SAEs and grade three (severe) experiences to determine if the episode represents an ongoing risk related to the study and make a determination about the subject’s further participation in the study. Grade 1 and 2 experiences will generally not be exclusionary unless they are related to the immunization and progressive in degree or persistent.

The decision to withdraw a participant may be made in the case of:

- Grade 4 adverse experiences
- Grade 3 adverse experiences related to the immunization and a determination that the duration or other factor indicates withdrawal is in the best interest of the subject
- Serious Adverse Experiences regardless of grade of individual event
- Grade 1 and 2 experiences related to the immunizations that are progressive in degree or persistent.
- HIV-1 infection
- Pregnancy

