## 10.2.7 ELISA based assay for RANTES production

## To culture lymphocytes (PBMC or MMC) for the detection of *in vitro* RANTES production, 4 x 104 to 4 x 106 cells are cultured in IL-2 (1000 units/ml) in 24 well, flat bottom plates (Becton Dickinson, San Jose, CA). For non-specific stimulation, PWM 10 ug/ml), PHA 5 ug/ml), or antibodies to CD2/2R and CD28 (Becton Dickinson, San Jose, CA) are added at 10 g/ml and 20 g/ml respectively. Antigenic stimulation will be performed as described above for ELISPOT. 1 ml supernatants are harvested at 24 hr, day 10, and day 14 and 1 ml of fresh media added. For quantitation, samples are diluted 1:2 in RPMI with 10% FCS and plated with 100 l of assay diluent (RD1A) on the RANTES ELISA plate (R&D Systems, Minneapolis, MN). When needed, supernatants have been further diluted 4-, 6-, or 10-fold. 100 l of standard provided in the ELISA Kit (R&D Systems, Minneapolis, MN) is added to the plate as well and incubated at room temperature for 2 hours. The plates are washed, conjugate is added at 200 l per well and the plate is incubated at room temperature for 1 hour. Plates are washed and 200 ml of substrate solution is added and the plates are incubated for 20 minutes at room temperature. 50 ml of stop solution is added and the plate is read at 450 nm on an ELISA reader (Spectra Max 340 from Molecular Devices, Sunnyvale, CA).

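### Section 8.4.2 ends trial participation, including safety follow-up, after a grade 4 event, and allows discretionary removal on baseline responses with no cut-off at randomisation

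*Protocol*

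**What the plan says.** - **Protocol Summary.** The target is "18 completing all visits to day 24 (completion of all baseline, vaccination, safety and immediate immune response visits". Enrolment, counted at signature of consent, may run "up to a total of 24 to allow for subject or investigator initiated withdrawal".
- **Section 8.4.2, grade 4.** "Experiences of grade 4 (potentially life threatening) will automatically exclude subjects from further participation in the trial". Later in the same section, a list introduced by "The decision to withdraw a participant may be made in the case of" has grade 4 experiences as its first item.
- **Section 8.4.2, baseline.** The investigator may withdraw a subject "because baseline responses will not permit an effective comparison with post-immunization results". No threshold is given, and no point in time after which this ground lapses.
- **Section 7.0.** "The randomization plan is based on three groups of six patients each". Each group of six splits into three groin and three deltoid, and each three into two active and one placebo. No allocation is described for a replacement.
- **Section 6.1.** "Twelve subjects will receive the vaccine, 6 in the groin area, subcutaneously (SQ) and 6 in the deltoid region intramuscularly (IM"; six more receive placebo, three by each route. Detection probabilities are given for 6, 12 and 18 patients.
- **Sections 4.1 and 5.0.** Participants are monitored for adverse experiences throughout the trial. Serious and grade 3 or higher events go on a report form within 48 hours, grade 4 and 5 events also go to the FDA and DAIDS, and lower grades are reported at the end of the study.

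**The concern.** Safety is the primary objective (section 1.1). A rule that closes participation after a grade 4 event stops planned observation in the subjects whose later course matters most for safety. Sections 8.4.1 to 8.4.3 describe no safety visits after such a withdrawal.

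The baseline-response ground raises a separate problem. The groin versus deltoid comparison has six vaccinees per arm and depends on randomisation. If a subject can be taken out after allocation, at discretion and without a criterion, by someone who knows the route, the arms being compared are no longer the arms that were randomised. The Summary counts completers and provides spare enrolment for these withdrawals, so nothing in the design discourages them.

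**Working it through.** **1. The plan's own figures.** With n patients and rate p, the chance of at least one event is 1 − (1 − p)^n. At p = 5%:
- n = 6: 1 − 0.95^6 = 0.265
- n = 12: 1 − 0.95^12 = 0.460
- n = 18: 1 − 0.95^18 = 0.603

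The visit-specific rows use four injections per subject (24, 48 and 72); for example, 1 − 0.99^24 = 0.214. All patient-specific rows, and the visit-specific rows from 1% to 30%, agree with the exact binomial to within 0.001. The table is correct for its n.

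**2. The enrolment buffer.** 24 − 18 = 6 consents, or 6/24 = 25% loss. Consent is signed at day −42.

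**3. What stops after a grade 4 event.** Take an event found at the day 3 visit. In the Summary of Studies table, the later adverse-experience assessments are at days 7, 10, 14, 17, 21 and 24 and months 6 and 12, eight in all. The later blood counts and chemistry panels are at days 7, 14 and 24 and months 6 and 12, five in all. Ending participation in the trial ends all of these.

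**4. When baseline results are in hand.** Section 10.2.4 gives ELISPOT two 24-hour incubations. Section 10.2.7 says "1 ml supernatants are harvested at 24 hr, day 10, and day 14", read here as days of culture. Sampling days are from the Summary of Studies; the first injection is on day 0.

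| Baseline sample | Assay | Result on study day | Against first injection |
|---|---|---|---|
| Blood and biopsy, day −28 | RANTES, last harvest | −28 + 14 = −14 | before |
| Biopsy, day −14 | RANTES, last harvest | −14 + 14 = 0 | same day |
| Blood, day 0 | ELISPOT | 0 + 2 = 2 at the earliest | after |
| Blood, day 0 | RANTES, three harvests | 1, 10 and 14 | after |

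Blood ELISPOT, chromium release, proliferation and RANTES have only two pre-vaccination samples, days −28 and 0. The second is drawn at the visit for immunization 1, so part of the baseline is known only after dosing. Section 7.0 randomises within cohorts of recruited subjects and does not place randomisation after the baseline visits.

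**5. Who can see the route.** Under section 7.0, study staff stay close by during vaccination. Under the Calendar of Studies, they examine the injection sites. The blind covers vaccine versus placebo, not groin versus deltoid.

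**6. Size of one removal.** 1/6 = 17% of a vaccine arm; 1/3 = 33% of a placebo arm. If the subject is neither counted nor replaced, detection at a 5% rate falls from 0.265 to 1 − 0.95^5 = 0.226 in one arm, and from 0.460 to 1 − 0.95^11 = 0.431 across vaccinees.

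**7. Allocations.** 3 × 6 = 18 places, all used by the planned 6/6/3/3. A subject who replaces someone already randomised has no described assignment.

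**The case against.** The strongest reply is that the Summary states a recruitment target, not an analysis set. Sections 4.1 and 5.0 keep grade 4 events monitored and reported, and section 8.4.2 ends participation without deleting the event. Analysis sets are commonly left to a statistical analysis plan, which is not at hand. Over-enrolment is counted at consent, six weeks before dosing, so much of the buffer will go on screen failures and pre-dose dropouts, who need no randomisation place. The day −28 results are available before dosing, and the calendar presents the baseline visits as screening. All of this stands, and it rules out three stronger readings.

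*That the worst outcomes vanish from the safety results.* A reader might infer this from the completer target. If the 12 vaccinee completers were the denominator, a grade 4 event before day 24 would be seen with probability 0, against 0.460 at a 5% rate. Two such subjects, both replaced, would read as 0/12 (95% upper limit 1 − 0.025^(1/12) = 26.5%) and not 2/14 = 14% (exact 95% interval 1.8% to 42.8%). No passage prescribes that analysis, so these figures are only a worst case. The 5% rate and the two cases are illustrative. Section 3.2 reports 6 severe local and 9 severe systemic reactions in about 420 volunteers (1.4% and 2.1%), and section 6.1 gives 0.006 for two or more events in 12 at a 1% rate.

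*That baseline-response withdrawal must happen after randomisation.* The text permits it then; it does not require it.

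*That section 6.1 is wrong.* It is not. If 14 vaccinees were dosed and counted, detection at 5% would rise to 1 − 0.95^14 = 0.51.

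The reply does not answer two points. The wording ends participation in the trial as a whole, and the baseline ground has no time limit.

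**Conclusion.** The point holds as two stated rules that would weaken the trial if followed: loss of scheduled safety observation after a grade 4 event, and criterion-free removal that can follow allocation. The first could cost up to eight adverse-experience assessments and five laboratory safety visits for an event found on day 3. The second puts 17% of a vaccine arm, or 33% of a placebo arm, at stake per subject removed. The unassigned replacement is a smaller gap that follows from the same passages.

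This rests on reading participation in the trial to include follow-up, and on the baseline including the day 0 blood sample, as the schedule shows. It does not rest on any claim that safety will be analysed in completers only. How often either rule would be used is not given, so no expected bias can be calculated.

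Section 8.4.2 also contradicts itself on grade 4: one sentence is mandatory and the list is permissive. The reporting text in section 5.0 likewise treats continued enrolment as something to be determined. These passages must be reconciled; which rule should apply is not a matter for this review.

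**What to change.** In the Protocol Summary, section 6.0 and section 8.4.2:

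- **(a) Safety denominator and follow-up.** State that every subject who receives at least one injection counts in the safety denominator of the assigned arm. State that, whatever rule governs further injections, withdrawal from injections does not end scheduled safety data collection, subject to the subject's consent.
- **(b) Baseline responses.** Restrict this ground to before randomisation, on results in hand by then, and allow no such removal afterwards.
- **(c) Replacement.** If a randomised subject is replaced, give the replacement the vacated allocation and report both subjects.
- **(d) Grade 4 wording.** Reconcile the mandatory and permissive statements in section 8.4.2.

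The cost is a few sentences of protocol text and a few extra follow-up visits. The safety denominator may exceed 18 and be slightly unbalanced across arms. The section 6.1 table can stay as it is, since it is correct for 6, 12 and 18.

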**NAME AND ADDRESS OF REVIEWING INSTITUTIONAL REVIEW BOARD**

Office for Protection of Research Subjects

UCLA Medical Institutional Review Board

[name]

[name]

1. **OBJECTIVES AND PURPOSE OF STUDY**

The goal of this vaccination study, using a randomized double-blind placebo controlled methodology, is to evaluate the safety and immunogenicity of ALVAC-HIV (vCP205) which contains the following inserted HIV-1 genes: the glycoprotein regions encoding gp120 (HIV-1MN) linked to the membrane-spanning portion of gp41 (HIV-1LA1), the genes encoding the entire Gag protein, and a portion of the Pol sequence (HIV-1LA1), sufficient to encode protease activity. The recombinant vaccine construct was developed by Virogenetics Corporation, Troy, New York. This experimental vaccine is manufactured by Aventis Pasteur S.A., Marcy L´Etoile, France. This experimental vaccine will be administered by subcutaneous injection in the groin (6 subjects), an area that drains to the inguinal lymph nodes to stimulate immunologic activity (locally) in the draining rectal mucosa as well as in the blood (systemically). Six subjects will receive the experimental vaccine intramuscularly into the deltoid region and will serve as the comparator arm of the study. In addition 6 subjects will receive placebo (3 groin and 3 intramuscularly)

**1.1 Primary Objectives**

To evaluate the safety of administering ALVAC-HIV (vCP205) vaccinations to healthy adult individuals using a subcutaneous targeted inguinal lymph node (TILN) or deltoid intramuscular vaccination at 1 x 106.87 TCID50 of ALVAC-HIV (VCP205) (Days 0,7,14 & 21)

**1.2 Secondary Objectives**

To compare the immunogenicity of subcutaneous (SQ) vaccination with four doses of ALVAC-HIV (vCP205) administered in the groin area versus four doses administered intramuscularly (IM) in the deltoid region versus four doses of placebo administered IM in the deltoid region or SQ in the groin area by determining whether successive immunizations induce increased levels of one or more of the following:

### CTL activity directed to canarypox and HIV-1 *env*, *gag* and a portion of the *pol–*gene products

### Anti-HIV-1 directed CD4+ T cell proliferative response to soluble p24 antigen

### CD8+ T cell specificity for HIV-1 epitopes

### Serum and mucosal immunoglobulins against HIV-1 epitopes

### Non-specific indicators of immune activation: -chemokine production, HLA-DR and CD38 on CD8 cells from blood and gut

1. **INTRODUCTION AND RATIONALE**

Human immunodeficiency virus type 1 (HIV-1) infection/AIDS has emerged as a worldwide public health problem associated with extensive morbidity and mortality. Although recent advances have been made in antiretroviral therapy against HIV-1, there is currently no cure. Ultimate control of the disease will likely depend on the development of a safe and effective vaccine against HIV-1.

HIV-1 is primarily a sexually transmitted disease1 that as of November 2002 has infected at least 42 million people worldwide since the beginning of the epidemic and at least 5 million people are infected annually2. It is most commonly transmitted via a mucosal surface. The mucosal lining itself is a primary potential site of both humoral and cellular protection consisting of B lymphocytes, activated memory T lymphocytes, secretory IgA, a host of antigen presenting cells (APC) including an extensive network of mucosal dendritic cells and baseline elevated levels of -chemokine expression3. The normal state of activity in the gastrointestinal mucosa is one of mild, controlled inflammation, which consequently provides increased viral targets. A protective vaccine will likely need to induce immune responses at the mucosal surfaces that are the portals of entry of HIV-1 into the body. Ideally, the vaccine would also induce systemic immunity so that virus that escapes neutralization by the mucosal immune response could be attacked by barriers of T lymphocytes and antibodies present in lymph nodes and blood.

The animal model that best mirrors human HIV-1 disease is simian immunodeficiency virus (SIV) infection of rhesus macaques. Previous work on mucosal immunity to SIV in the rhesus model has guided the development of the current protocol. The current protocol is designed to reproduce in humans knowledge learned from the SIV model, in particular, that delivery of immunogen to the groin area can confer protection against SIV infection in a sexual transmission model, while the same immunogen delivered by other routes fails to protect. Total protection against transmission of SIV across the rectal mucosa was achieved in 4 of 7 macaques and partial protection was achieved in the remaining 3 of 7 when immunogen was delivered by targeted iliac lymph node immunizations. Infection occurred in 13 of 14 unimmunized macaques or those immunized by other routes4.

The targeted lymph node route of immunization involves vaccine injection into the subcutaneous tissue near a lymph node. This efficiently uses the host’s antigen presenting cells to deliver antigen to the lymph node where specific immune responses develop that subsequently may protect the host from infection with the pathogen. The iliac and inguinal lymph nodes are the primary draining lymph nodes of the genitourinary and rectal tracts 5,6. Therefore, this protocol will use groin immunizations (SQ, Inguinal region) as the site for delivery of immunizing antigen to nodes draining the rectal mucosa. As the axillary and supraclavicular lymph nodes are those primarily draining the deltoid area and these nodes do not drain rectal mucosal surfaces, their associated non-mucosal drainage region (IM deltoid) will be used as a comparative immunization site/route. No sampling of nodes is planned in this study.

In the SIV/macaque model, protection against rectal challenge was associated with a significant increase of sIgA-secreting cells in the lymph nodes and of sIgA at the mucosal surface, and increases in CTL activity, CD4+ specific T cell proliferative responses to *gag* proteins and CD8-suppressor factor and -chemokine production from blood mononuclear cells and autopsy mucosa. The immunization thus provoked immune responses on three levels of immunity: mucosal, in draining lymph nodes, and in the circulation. These responses may all contribute to more complete protection of the host against viral challenge. While secretory IgA and -chemokines operate at the mucosal surfaces, in the lymph nodes or circulation, alternate mechanisms including CTL activity may play the pivotal role if the mucosal barrier is breached.

In our protocol, the routes (subcutaneous and IM) of administration of the vaccine has been previously used in prior ALVAC-based vaccine trial subjects7 only the site (groin area) is novel. This site was selected in order to stimulate an immune response in the inguinal nodes, which serve as an inductive site to sensitize lymphocytes that home to the mucosa. The route of immunization typically used for vaccines, i.e., immunization in the skin of the arm, is associated with induction of systemic immunity (i.e., immunity detectable in the blood) but has not been evaluated for induction of mucosal immune responses. This is because the inductive sites for mucosal immune responses are separate from those for systemic immunity. Evidence that the site of immunization is critical for protection against transmission of HIV-1/SIV across at least the rectal mucosa is provided by the results of a previous study in monkeys where immunization by conventional routes did not confer protection against rectal transmission, while immunization by targeted lymph node immunization in the groin area did confer protection4.

One hundred and fifty-one non-ALVAC-HIV (vCP205) inoculations into the groin area of 37 macaques have been done in the course of [name] studies using combinations of immunogens and/or adjuvants with no adverse events. Thus, groin immunization itself is thought to be safe and there is no reason to expect that ALVAC-HIV (vCP205) inoculation into this site in humans, rather than the arm would cause specific safety concerns.

Building on prior protective immunizations in the non-human primate model following targeted lymph node immunizations, we will determine whether a similar HIV-1 immunization strategy in humans elicits potentially protective immune responses in the blood and in the rectal mucosa. By targeting our vaccine to the mucosal immune system, we expect to successfully stimulate a detectable memory CD8+ T cell response as well as local immunoglobulin production in all of our subjects. This, coupled with the primary endpoints of safety, would represent desirable endpoints for this Phase I study.

